### 6. Ethics approval and consent to participate

This protocol explains a study that is being done as part of the data utilization initiative. The protocol received ethical clearance certificate from National Health Research Ethics Committee (NaTHREC),Ref. NIMR/HQ/R.8a/Vol.IX/3940.Permission to collect data in the regions and councils will be sought from the President’s Office Regional Administration and Local Government, the Ministry of Health(MOH), the Regional Secretariat (RS), and the Local Government Authorities (LGAs). All study participants will be asked to provide written informed consent. In publications resulting from this study, no personally identifying information will be disclosed.

### 7. Dissemination

The results from the current study will be shared with participating districts and health facilities, disseminated through scientific conference presentation and peer reviewed journals. Authorship of the resulting papers will be decided based on the International Committee of Medical Journal Editors criteria.

## Discussion

Data use initiatives are among the most complex health system interventions implemented at different levels in the health care settings. The interventions in the course of implementation, required articulation of processes and inputs along multiple levels (district, health facility to individual frontline health care workers), actors and actions that required also support and continuous technical backstopping from different levels and actors.

This study represents a first attempt to document the implementation process, determine the implementation outcomes, understand the determinants of implementation processes and outcomes and determine the effects of data use initiatives on quality of care and health outcomes.

Our implementation-effectiveness hybrid design that takes a before and after controlled design to determine the effects of data use initiatives while also understanding the counterfactual is expected to provide a holistic picture on the interaction between implementation outcomes and program outcomes [24]. The mixed methods design that takes into consideration the implementation process and outcomes amid the influence of contextual factors, is envisaged to provide a comprehensive picture of the influencers of the implementation processes as documented in existing evidence [34].

The current study is designed to yield the best possible evidence to guide implementation of data use initiatives in the primary health care settings. The development of the TOC and monitoring and evaluation framework that saw a combined team of program developers, implementers and researchers, represents a best practice in designing implementation-effectiveness hybrid studies as proposed also in previous evidence in implementation research [35].

The use of mixed-methods approaches as well as multiple tools of collecting data will enable the development of recommendations to improve future implementation of the data use initiatives and other implementation studies of similar nature by identifying trends, challenges and potential solutions to implementation challenges amid contextual influences as well as design issues if they exist. We must also acknowledge the limitations that this study may prone to missing data as well as recall bias as collection of data will take place some months after start of the data use interventions.

Although, we will apply matching in the course of selecting the intervention and control facilities, the fact that we will recruit primary health facilities across the four regions which vary in size, geography, population served, there may be some variations in outcomes. Moreover, although the before–after controlled studies can help overcome the problem of confounding, there is always a risk of unidentified confounders when there is no randomization thus leading to some risk for confounding or bias [36].

This protocol was developed amid the challenges of COVID-19 pandemic that limited face to face meetings. We managed to minimize face to face encounters and relied on virtual communications that could have some effects on same decisions. The various waves of the Covid-19 that presented differently were seen as barriers to face to face meeting and therefore rely on web-based platforms.

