Based on the PRISM (*Performance of Routine Information Systems Management*) framework, for data use intervention to be effective, they should address inputs, processes and outputs or performance of routine health information systems (RHIS) [14]. The PRISM framework defined RHIS performance as better quality data and continuous use of information. RHIS performance is a function of RHIS processes and their technical, behavioral and organizational determinants. Addressing these determinants may lead to improved quality of care, better health outcomes and system performance.

In Tanzania, UNICEF and the Data For Implementation (Data.FI) project, funded by the United States Agency for International Development (USAID), are implementing a data use initiative in the primary health care settings with a goal of improving data use in decision making and planning at different levels, Data.FI providing support at the council level while UNICEF in collaboration with PORALG providing support at the facility level. The interventions are implemented in the two regions of Tanzania namely Dar es Salaam and Dodoma, in which two local government authorities (councils) in each of the region have been recruited in the intervention.

Interventions to address data use in primary health care settings are often complex with multiple components. Complex interventions require extensive stakeholder involvement, longer time frames, and are subject to strong contextual influences [15, 16]. As a result, they pose evaluation design and implementation challenges, necessitating a comprehensive approach to program evaluation and monitoring. Desirable evaluation designs are those that aim at: 1) understanding the implementation processes of the intervention and the moderating factors, specifically describing in detail the adoption, fidelity program reach, beneficiaries/client responsiveness and quality of implementation of key process indicators as well as sustainability indictors 2) Using the implementation outcomes to explain the probable variations of effects observed when measuring the impact of the program.

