#### b. Description of the data use initiatives

This implementation study is conducted in the context of an intervention that is set to promote data use for decision making and planning to improve the quality of care and health status (outcomes) of the population.

The President’s Office ‐ Regional Administration and Local Government (PO-RALG) requested assistance from UNICEF and USAID to promote and institutionalize a culture of data use at subnational level in the stride forwards to achieve universal health coverage (UHC) and strengthen PHC systems in line with the decentralization policy and related approaches such as the direct health facility financing (DHFF) . USAID engaged the Data for Implementation (Data.FI) project, to support the implementation of the request with the aim of using quality data to support evidence-based health programming and accountability.

In April 2021, UNICEF and Data.FI drafted a proposed joint implementation plan to support implementation of data use for this quality improvement initiative at different levels of the health care system, with Data.FI, providing support at national, regional and council level whereas UNICEF supports the health facility level. The intervention strategies aim to address 1) organizational determinants of data use (governance, equipment & tools and planning ) 2) technical determinants of data use (physical infrastructure, ICT infrastructure , HIS design and operability 3) behavioral determinants of data use (capability, opportunity and Motivation )

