### 2. Study design

This study will adopt an effectiveness-implementation type-2 hybrid design [22] to evaluate the effectiveness of the data use initiatives in improving quality of health service delivery and health outcomes while simultaneously understanding the implementation of the initiatives. Since the data use initiative is implemented in twenty health facilities of two regions, we plan to carry out a before and after controlled design to estimate the combined effects of the data use initiatives in the intervention sites and matched control regions. Simultaneously we plan to assess the implementation processes of the initiatives and this entails the integration of both quantitative and qualitative data collection, analysis, and interpretation methods (i.e. mixed methods) to understand the implementation processes and the influencing factors.

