### 4. Study components

The steps to conduct this study will be based on the two main components of the study, that is , effectiveness and implementation process .The effectiveness component entails collecting data to measure outcomes of the initiatives on selected indicators (top level indicators for service areas such as maternal, newborn, adolescents and child health ) at PHC before and one year after the implementation of the program .The implementation process study aims at understanding how the program is implemented amid contextual influences. To complete the components, the study will adopt the following steps.

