To assess the extent of adoption of the data use initiativesTo determine number or proportion of beneficiaries reached by the data use initiativeTo assess the fidelity to data use initiative protocol and SOPsTo assess acceptability of the data use initiative by primary beneficiaries and other stakeholdersTo assess sustainability of the data use initiative in the intervened primary health facilitiesTo determine the implementation challenges and success of the data use initiativesUnderstand the effects of the data use initiative on health system and patient outcomes

To understand the effects of the data use initiative, we will collect data at baseline and end line in order to allow two points measures of the outcome data. In this step, to assess compliance to national and international quality standards, the study team will rely both on the analysis of the routine health information system (at the facility level and district level) and information collected from respondents. Specific research questions include, i) has the quality of primary health facility data improved following implementation of the initiative? ii) What factors have contributed to the observed changes?

Specific objectives:-

Assess the effect/impact of data use initiative on beneficiaries’ capabilities (knowledge, and skills to analyze and interpret data)To evaluate the impact/effect of data use initiative on the quality of data collected in the primary health facilitiesTo determine the impact/effect of the initiative on the use of data for decision making and planningTo evaluate the effect of data use initiative on the performance of primary health facilities in terms of quality of delivered health services (availability drugs, medical supplies and equipment) and client’s satisfaction with the services.

*Study component 1*: *Measuring effects of the data use initiative*. This component aims at establishing the effects of data use initiatives on quality of care and selected health outcomes. To establish and control the counterfactual, data will be collected in the intervention and control councils. This component comprises collection of quantitative and qualitative data at two points (baseline and end line) covering a period of one year.

*Sampling and sample sizes*. This component will collect information from health facility documents , health care workers, and patients. The samples and sample sizes for this quantitative component are as follows

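### The limitations place data collection some months after the interventions start, the design needs a pre-start baseline, and no date reconciles them; the two-point DHIS2 plan cannot show prior trends

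*Protocol article*

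**What the plan says.** Section 2 (Study design) sets the framework: "we plan to carry out a before and after controlled design to estimate the combined effects of the data use initiatives". Section 4 (Study components) times the outcome measurements "at PHC before and one year after the implementation of the program". Under Study component 1 the span is described a little differently: "This component comprises collection of quantitative and qualitative data at two points (baseline and end line) covering a period of one year".

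The limitations paragraph of the Discussion then states that "collection of data will take place some months after start of the data use interventions", and names missing data and recall bias as the consequences. It does not say which round or tool is meant.

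On the state of the programme, the Introduction says that the partners "are implementing a data use initiative in the primary health care settings". The only programme date is in section 1b: "In April 2021, UNICEF and Data.FI drafted a proposed joint implementation plan". That is the date of a draft plan, not of a start.

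For outcome data generally the plan is that "we will collect data at baseline and end line in order to allow two points measures of the outcome data". For the DHIS2 extraction form, Table 2 lists descriptive statistics, cross-tabulation and a paired t-test of baseline against end line.

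**The concern.** A controlled before-and-after study takes its effect from the change since an unexposed baseline. If the sentence in the limitations covers the baseline round, the intervention councils are partly exposed when first measured and the control councils are not. Part of the effect is then subtracted from itself, and the contrast probably moves towards no effect. The limitations name missing data, recall bias and unidentified confounding, but not this.

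The second issue is separate and ranks lower. Councils were chosen purposively. Controls were matched on urban versus rural location, and both councils described as metropolitan (Temeke and Kinondoni) are in the intervention arm. Different trends before the start are therefore plausible. One value before and one after cannot reveal them, and a paired t-test compares two times without comparing the arms.

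**Working it through.** The plan gives no power, effect size or timing figure for this contrast, so there is nothing of its own to reproduce. The two sample sizes it derives (440 health workers, 422 patients) do not depend on timing. The check is a comparison of passages, followed by illustrations on stated assumptions.

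**1. Passages side by side**

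| Place | What it implies for the baseline |
|---|---|
| Section 2; section 4 | Before implementation |
| Study component 1, data collection tools (organizational readiness tool piloted at baseline) | Before implementation, by implication |
| Section 1, Study settings (future tense for the intervention) | Before implementation, by implication |
| Introduction (present tense) | Open: programme already running, no date |
| Discussion, limitations | After start, if the sentence covers every round |

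No start date and no baseline date appears, so the article does not settle the matter.

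**2. Size, if the baseline were late**

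Assumed: baseline at month *m* after start, with *m* = 3 or 6 (the article gives no number). From section 4: end line at month 12.

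- Linear build-up: share kept = 1 − *m*/12. For *m* = 3, 1 − 3/12 = 75%. For *m* = 6, 1 − 6/12 = 50%.
- Build-up with half-life *h*: e(t) = 1 − 2^(−t/h), share kept = [e(12) − e(*m*)]/e(12). With *h* = 6 months: (0.750 − 0.293)/0.750 = 61% at *m* = 3 and (0.750 − 0.500)/0.750 = 33% at *m* = 6. With *h* = 3 months: (0.9375 − 0.500)/0.9375 = 47% and (0.9375 − 0.750)/0.9375 = 20%.
- End line delayed equally, to month *m* + 12, as the one-year span under Study component 1 would allow: with linear build-up continuing, the increment is [(*m* + 12) − *m*]/12 = 1, so nothing is lost. If the effect levels off at month 12, the share kept returns to 1 − *m*/12.

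The loss therefore runs from none to 80% over these assumptions.

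**3. Two-point DHIS2 measurement**

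Assume the arms were already diverging by *b* standard deviations per month. A two-point difference in change over 12 months carries a bias of 12*b*: 0.12 SD for *b* = 0.01 and 0.36 SD for *b* = 0.03. Nothing in two points shows this.

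**4. Check on the remedy**

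Averaging follow-up over months 0 to 12 would bring in a dilution of its own. Under linear build-up the mean effect over that window is (0 + 1)/2 = 50% of the month-12 effect. The follow-up window has to sit around end line, or time since start has to be modelled.

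**The case against.** The benign reading is the more likely one. Recall bias fits people looking back on implementation, as at the 6-month follow-up or at end line, better than a baseline of current status. The readiness tool and the future tense in the settings section point to a baseline before start, and the present tense in the Introduction can be read as a description of the programme. A reader might infer that the baseline was in fact taken after the start; the documents do not support that. What stands is that the sentence carries no restriction and that no date contradicts it.

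Two points are also what a controlled before-and-after study ordinarily has, and the Discussion concedes unidentified confounding. Most DHIS2 indicators are counts, so each point must cover some window, which an article may leave to the full protocol. Section 5 mentions regression in general terms. These points make the DHIS2 issue a design weakness rather than a contradiction. They do not supply a trend check, and regression is not among the techniques that Table 2 lists for the DHIS2 form.

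A reader might further infer that a clean pre-start series is available at almost no cost. The article gives no DHIS2 reporting frequency, look-back, completeness or extraction cost. It does say that the records are electronic and that facilities had operated for more than a year. A pre-start series would be unexposed, but not necessarily clean: data quality is itself an outcome of the initiative, so a change in reporting can look like a change in health.

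**Conclusion.** The timing statements conflict as written and must be reconciled. Whether the baseline is exposed cannot be decided from the article, and a late baseline is the less likely reading. If it is late, the bias is probably towards no effect. The figures of 75% and 50% kept (months 3 and 6) rest on assumed months, linear build-up and an end line at month 12. They are illustrations and should not be read as an estimated loss.

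The two-point DHIS2 plan with a paired t-test is a secondary weakness that stands whichever way the limitations are read: the test does not contrast the arms, and two points cannot show diverging prior trends among four purposively chosen councils per arm.

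**What to change.** - State the intervention start date for each council and the baseline date for each tool, and say which round the sentence in the limitations refers to.
- Where a survey baseline falls after start, give the number of months and report that contrast as early-versus-late.
- For DHIS2, extract the available periods (monthly if reported so) from at least 12 months before start through end line in all 80 facilities. Table 2 lists 40 facilities and 4 districts for this form, while the Abstract has routine data from all 80, so confirm that both arms are covered.
- Check reporting completeness by arm and period before analysis.
- Fit arm by period, allowing for clustering by facility and council, with a pre-trend check.
- Estimate the one-year effect from the months around end line against the same calendar months before start, or model time since start. Do not average months 0 to 12.

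The cost is wording, a wider extraction window and some analysis work. Since the records are electronic, no new fieldwork should be needed, although the article does not state the effort. The DHIS2 series cannot repair a late baseline for the survey or star-rating outcomes, and changes in reporting quality may affect the series itself.

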#### a. Study sites

The intervention districts will be selected purposively based on the fact that the data use interventions will be implemented. The control districts will be selected from two regions to match the intervention districts based on geographical location (urban vs. rural). The health facilities from the selected districts were selected based on the following criteria: a primary public health facility, providing services for more than a year. Hereunder the characteristics of the selected districts are described.

Kinondoni and Temeke are urban districts (Municipality) in the Dar es Salaam Region, the business capital of Tanzania Mainland. The census of 2012 showed that the population of Kinondoni was 1,775,049 whereas that of Temeke District is 1,368,881.

Chamwino and Dodoma City councils are districts in Dodoma Region, the administrative capital of the united republic of Tanzania. The census of 2012 showed that the population of Chamwino was 330,543, whereas that of Dodoma city council was 410,956.

Tanga city council and Korogwe are districts in the Tanga region, one of the important cities in the coastal zone of the country. The census of 2012 showed that the population of Korogwe was 56,282 whereas that of Tanga city council was 273,332.

Mwanza city council and Misungwi District council are districts in Mwanza region, one of the important cities in the Lake zone region of the country. The census of 2012 showed that the population of Mwanza city council was 706,453 whereas that of Misungwi was 351,607.

The eight councils represents a mixture of metropolitan (Temeke & Kinondoni), urban (Dodoma City council, Mwanza city council, Tanga city council) and rural district councils (Chamwino, Korogwe and Misungwi). The study areas are suitable of generating outcomes that could easily be transferable to other similar settings in the country.

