#### 2) Understand the initial (baseline) situation of data use in the study settings in relation to decision making and comprehensive (council or health facility) planning

To understand the baseline situation, the four councils implementing the data use initiative will be matched equally with comparable councils where the data use interventions will not be implemented. Stratified sampling (to distinguish the level of facilities) will be used in these four councils to select a representative sample of facilities to be observed for one year after the project is implemented. This step combines quantitative and qualitative methodologies to evaluate the current state of data use in the recipient health facilities.

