### 5. Analytical procedures

Descriptive analysis will be used to summarize data where by continuous data will be summarized using mean and standard deviation (SD) as well as medians and interquartile range. Dichotomous variables will be summarized using frequency and percentage. Chi-square test or fisher exact will be used to evaluate bivariate associations between categorical variables where by t-test will be used to estimate association in numeric variables and ascertain whether there mean different between categories. We will also use regression analysis.

Audio-recordings of in-depth interviews and focus group discussions will be transcribed verbatim in Kiswahili guided by a transcription guideline and translated to English. Transcription and translations will be done by the research team that conducted the respective IDIs. Codes will be grouped into categories, sub-themes and themes. Thematic analysis will be used to analyze qualitative data using ATLAS.ti 8 software. Table 2 provides details on data collection tools, administration, sample size and analytical techniques.

**Table 2 pone.0303552.t002:** Data collection tools, administration, sample size and analytical techniques.

S/N	Data collection tool	Level (s) of administration	Method of administration	Sample size (effects measurement)	Sample size (process evaluation)	Analytical techniques
1	Document review checklist	CHMT and Health facility level	physical and e-records, in ODK	Health facilities (N = 40), Districts (N = 4)	Health facilities (N = 20), Districts (N = 2)	Descriptive statistics on frequency, mean and standard deviation, Cross tabulation to compare performance of the participants
2	Semi structured interview guides for in-depth interview	All levels (national, regional, district, health facility, community representatives)	face to face	Patients, dispensary (N = 32), Patients, health center (N = 32), Health care workers, Dispensary (N = 16), Health care workers Health centers (N = 16),	Health facility governing committee members (N = 80), CHMT members (N = 60), RHMT members (N = 4), implementing partners (N = 4)	Thematic analysis will be used to analyze qualitative data using ATLAS.ti 8 software

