3	Structured questionnaire	Health facility level	Face to face (guided), in ODK	Health care workers (N = 440), exit patients (N = 422)	Health care workers (N = 200)	Descriptive statistics (mean, standard deviation), Cross tabulation to compare groups’ performance Regression analysis for checking statistical significances among and between the participants Paired sample t test for comparing means between the baseline and end-line surveys
4	DHS2 extraction form	Health facility level / District level	electronic records	Health facilities (N = 40), Districts (N = 4)		Descriptive statistics on frequency, mean and standard deviation, Cross tabulation to compare performance of health facilities/ districts, Paired sample t-test for comparing means between the baseline and end-line surveys

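### The analysis named for the DHIS2 health outcomes uses neither the urban/rural match, facility level nor facility volume, although the matched councils are unbalanced on the matching factor

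*Protocol article*

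**What the plan says.** Matching is applied at selection. Under Study sites: "The control districts will be selected from two regions to match the intervention districts based on geographical location (urban vs. rural"). The baseline step adds that "the four councils implementing the data use initiative will be matched equally with comparable councils", with facilities sampled by level. The Discussion repeats that "we will apply matching in the course of selecting the intervention and control facilities", and then accepts as a limitation that the study will "recruit primary health facilities across the four regions which vary in size, geography, population served, there may be some variations in outcomes".

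Section 5 (Analytical procedures) states that "Chi-square test or fisher exact will be used to evaluate bivariate associations between categorical variables", with t-tests for numeric variables, and adds one general sentence that regression will also be used. In Table 2, the questionnaire row (row 3) lists regression as a check of significance among participants. The DHIS2 row (row 4) does not list it. Beyond descriptives, row 4 gives: "Cross tabulation to compare performance of health facilities/ districts, Paired sample t-test for comparing means between the baseline and end-line surveys".

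Study sites classifies the councils as "metropolitan (Temeke & Kinondoni), urban (Dodoma City council, Mwanza city council, Tanga city council) and rural district councils (Chamwino, Korogwe and Misungwi") and gives the 2012 census population of each.

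**The concern.** Without randomisation, the urban/rural match is the design's main protection at selection, and the protocol itself says the sites still differ. For the health outcomes, the listed methods do not carry the match or the recorded site factors into the comparison of arms. The paired t-test pairs over time, not between matched sites. Cross-tabulation could set arms side by side, but without adjustment.

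If urban and rural facilities change at different rates for reasons unrelated to the initiative, an uneven urban/rural mix turns that difference into an apparent effect. For raw counts, facilities of unequal volume show unequal absolute change even when their proportional change is the same. Both could be read as an effect of the initiative on deliveries, antenatal visits or HIV testing.

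**Working it through.** The protocol gives no figure for this contrast, so there is none to reproduce. The check uses its own site list.

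**Inputs.** Council types and populations come from Study sites. Ten facilities per council come from Study settings, and 40 facilities per arm from the sampling section. Table 2's 40 facilities and 4 districts are read here as per arm. The DHIS2 indicators come from the data collection tools.

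**1. Balance on the matching factor.**
- Intervention: Temeke and Kinondoni metropolitan, Dodoma City urban, Chamwino rural. Urban or metropolitan share = 30/40 = 75%.
- Control: Tanga City and Mwanza City urban, Korogwe and Misungwi rural. Urban share = 20/40 = 50%.
- Gap = 0.75 − 0.50 = 0.25. The council mix is 3:1 against 2:2.

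**2. Bias of an unadjusted contrast of changes.** Let rural facilities change by s without any intervention, and urban or metropolitan ones by s + d. With a true effect of zero:
- intervention mean change = 0.75(s + d) + 0.25s = s + 0.75d
- control mean change = 0.50(s + d) + 0.50s = s + 0.50d
- contrast = 0.25d

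The protocol does not give d. Over an assumed range:

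| d (points) | 2 | 5 | 10 | 20 |
|---|---|---|---|---|
| Bias (points) | 0.5 | 1.25 | 2.5 | 5.0 |

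Example: s = 5 and d = 10 give 12.5 against 10.0, a spurious 2.5. Within urban and within rural facilities the contrast is 0, so adjusting for type removes this component. Facility level works the same way, as (gap in share) × (difference in change), but the article does not give the level mix by arm.

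**3. Counts and volume.** Five of the six DHIS2 indicators are numbers of events or women (deliveries, fourth antenatal visits, women tested, women HIV-positive, maternal deaths). Only the ARV indicator is a proportion.
- Intervention population: 1,775,049 + 1,368,881 + 330,543 + 410,956 = 3,885,429.
- Control population: 56,282 + 273,332 + 706,453 + 351,607 = 1,387,674.
- Ratio = 2.80.

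The article gives no facility volumes. Purely as an illustration, suppose that volume followed this ratio. A common 5% growth on 280 and 100 deliveries gives +14 and +5, an apparent effect of 9. As ratios, 294/280 = 105/100 = 1.05, and the contrast disappears.

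**4. What adjustment cannot reach.** Dar es Salaam and Dodoma lie wholly in the intervention arm, Tanga and Mwanza wholly in control. Metropolitan councils are 2 against 0. Both have populations ("the population of Kinondoni was 1,775,049 whereas that of Temeke District is 1,368,881") above the largest control council, at 706,453. If metropolitan facilities have an extra trend m, the urban stratum still carries (20/30) × m after adjustment for urban/rural type.

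**The case against.** The strongest reply is that the article does name regression, once without restriction by outcome and once in the questionnaire row. A covariate list is commonly left to a fuller plan. This stands for the questionnaire outcomes: adjustment there is unspecified, not excluded. A reader might infer that every comparison is bivariate, and the text does not support that. It does not fully answer the DHIS2 row, where the methods are listed and regression, present one row above, is absent.

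Second, fixed differences between sites cancel in a controlled before-and-after contrast, and the paired test uses each facility's baseline by differencing. This is correct on an additive scale. A reader might take the 2.8-fold population difference as the size of the bias; it is not, because only differing change biases the contrast. For raw counts, however, unequal volume itself produces differing absolute change.

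Third, balance achieved at selection protects even an unadjusted contrast. That is also true, but the listed councils are not balanced, and the whole bias in step 2 comes from that gap.

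Fourth, a reader might conclude that the conceded bias is removable. Only part of it is. Region and metropolitan status cannot be separated from arm, and the Discussion's warning about unidentified confounders is sound. Any gain in precision from adjustment would also depend on differences between facility levels that the article does not report.

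**Conclusion.** The point holds chiefly for the DHIS2 health outcomes. The methods listed for them include no between-arm analysis that uses the matching factor, facility level or facility volume, while the council list shows 75% against 50% on the matching factor. The bias of an unadjusted contrast of changes is 0.25d, or 2.5 to 5 points for an assumed d of 10 to 20 points, and zero if urban and rural trends are equal. The 0.25 follows from the protocol's own list and ten facilities per council; d is an assumption. The volume effect for counts is certain in direction only where facility volumes differ between arms, and the article gives no volumes to size it. For questionnaire outcomes the gap is narrower: the regression is named but not linked to these factors. The documents do not support saying that adjustment is ruled out throughout, or that it would leave only unmeasured differences. It is worth correcting because the remedy uses data already planned for collection.

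**What to change.** 1. Add regression to Table 2, row 4. State that each DHIS2 effect is the intervention-minus-control contrast in baseline-to-end-line change, adjusted for urban/rural type and facility level (dispensary or health centre). If both rounds are stacked in one model, these factors must enter with their interaction with round; main effects alone do not adjust for differing trends.
2. Model counts relative to the facility's own baseline volume, on a log or rate scale. Where zero counts are likely, as for maternal deaths, use a count model instead of logged facility ratios.
3. Use the same covariates in the questionnaire regression, again as an arm contrast in change. Conditioning on a facility's mean among exit patients would be a poor substitute: if 422 are interviewed per round, it rests on about 422/80 ≈ 5 people.
4. Keep chi-square, Fisher and t-tests as description.
5. Keep the caution in the Discussion and add that region and metropolitan status are fully confounded with arm and cannot be adjusted away. It should not say that only unmeasured differences remain.

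Cost: analysis wording, with no new data. Urban/rural type varies only between the eight councils, so it uses council-level information. With the council as the unit, residual degrees of freedom fall from 8 − 2 = 6 to 8 − 3 = 5. Facility level costs one of the 80 facilities' degrees of freedom.
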